**Methods:**

Two communities will use the SEED Method and one will use a modified Delphi method. We aim to recruit a total of 144 participants (48 per community). The evaluation team will randomize participants to an intervention group or a control group. In addition, we will collect outcome data from the participatory research team members leading the projects in each county (*n* = 18) and from additional community members who participate in focus groups (*n* = 32). The primary outcome for all participants will be the change in self-reported civic engagement as measured by the total score on the Individual Mobilization Scale.

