### Research questions

Are there differences in outcomes between engagement approaches (SEED and Delphi)?Are there differences between the intervention and control groups on the following key outcome variables?

Civic engagement (mobilization, motivation, and participation).Strategy development (the number, type, and diversity of strategies created).

The hypothesis is that higher levels of engagement will result in greater change in civic engagement and greater diversity in proposed strategies.

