### Outcomes measures

The primary outcome for all participants, civic engagement, will be measured as the total score on the Individual Mobilization Scale [37]. Mobilization refers to individual empowerment and human capital that facilitate contributions to community change. The Mobilization Scale, and the related Individual Community Related Empowerment Scale (ICRE), have been tested in several previous studies, [38, 39] and are being used as outcome measures of empowerment and social agency in additional protocols [40, 41]. This scale contains 24 questions in the categories of human capital, social assets, self-efficacy, motivation, and participation. The response categories for the questions are strongly disagree, disagree, not sure, agree, and strongly agree.

Secondary outcomes include Mobilization Scale subscores for motivation and participation, as well as key outcome indicators (number, types, and diversity of strategies developed) and process indicators. To collect these data, the pre- and post-surveys also cover demographics, group dynamics (e.g., perceptions that participants are able to speak openly and honestly, team members respect each other’s point of view, opinions are listened to and considered by other team members, all team members are made to feel welcome, and the team has been successful implementing project tasks), and group processes (e.g., satisfaction with meeting facilitation, how the team works, the way the team deals with problems, meeting location, meeting times, and compensation).

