### Sample size and power analysis

**Table 3 Tab3:** Number of planned participants by site and intervention type

	Site 1 (SEED Method)	Site 2 (SEED Method)	Site 3 (Delphi method)
**Intervention**	24 (3 groups of 8)	24 (3 groups of 8)	24 (1 group, with number of specific stakeholder groups TBD)
**Control**	24	24	24

The power analysis is calculated based on the sample sizes of the intervention and control group participants only. A target number of 48 participants per community will be recruited and randomized to the intervention or control condition (24 per condition) (Table 3). Minimal detectable differences between the variables of primary interest were estimated with this sample size, setting the alpha error at 0.05 and the beta error at 0.20, adjusting for the estimated ICC and the usual population variances based on cited research (Table 4). Based on these analyses, the anticipated sample size will have an 80% probability of detecting treatment differences in the primary outcomes if the true differences are in the range of the minimum detectable differences. These scores were calculated based on the standard deviations reported by Kasmel and Tanggaard [38].

**Table 4 Tab4:** Minimum detectable differences (MDD) in primary outcome variables

Minimum Detectable Difference (MDD) and Percent Minimum Detectible Difference (%MDD)			
Estimated *n* = 144	$$\:\underset{\_}{x}$$ ^*^	SD^*^	MDD (%MDD)
Mobilization Scale (Total)	1.87	0.37	0.12 (6.5)
Participation Subscale	1.70	0.56	0.18 (10.9)
Motivation Subscale	1.83	0.56	0.18 (10.1)

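### The power section and Table 4 call two subscales primary that the outcomes section makes secondary, so the protocol states its confirmatory outcome in two incompatible ways

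*Protocol article*

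**What the plan says.** The section on outcome measures defines a single primary outcome: "The primary outcome for all participants, civic engagement, will be measured as the total score on the Individual Mobilization Scale". The Methods paragraph of the abstract agrees and expresses it as the "change in self-reported civic engagement as measured by the total score on the Individual Mobilization Scale". The outcomes section then ranks the subscales: "Secondary outcomes include Mobilization Scale subscores for motivation and participation".

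The section on sample size and power ranks them differently. Table 4 carries the title "Minimum detectable differences (MDD) in primary outcome variables" and has three rows: the Mobilization total, the Participation subscale and the Motivation subscale. The text above the table promises an "80% probability of detecting treatment differences in the primary outcomes", in the plural, after "setting the alpha error at 0.05 and the beta error at 0.20". It gives no division of alpha among the three rows.

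The research questions and the section on evaluation activities list mobilization, motivation and participation side by side without ranking them. The data analysis section applies one longitudinal model to primary and secondary outcomes. It keeps the two tiers apart in name but does not say which variable belongs to which.

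**The concern.** The same two variables are secondary in one section and primary in another, and both statements are current text. A reader who wants to know which result is confirmatory gets one answer from the abstract and the outcomes section and another from the power section.

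This matters most for a split result. If Participation or Motivation moved and the total did not, the power section could be cited for calling that a primary finding, and the outcomes section for calling it secondary. Each Table 4 row also appears to use the full 0.05, so treating all three as primary would carry more type I error than a single primary test.

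**Working it through.** **1. The labels side by side**

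| Variable | Abstract and outcomes section | Power text and Table 4 |
|---|---|---|
| Mobilization total | primary (the only one) | primary |
| Participation subscale | secondary (outcomes section) | primary |
| Motivation subscale | secondary (outcomes section) | primary |

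Two of the three rows conflict.

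**2. Which alpha lies behind Table 4**

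Inputs from Table 4: means 1.87, 1.70 and 1.83; SDs 0.37, 0.56 and 0.56; stated MDDs 0.12 (6.5%), 0.18 (10.9%) and 0.18 (10.1%). Alpha is 0.05 and power 0.80. Sidedness is not stated; two-sided is assumed.

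Formula: MDD = (z for alpha + z for power) × SD × √(2/n per arm). At two-sided 0.05 and 80% power the multiplier is 1.960 + 0.842 = 2.802.

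The table's figures come back when 144 is entered as the number per arm:
- Total: 2.802 × 0.37 × √(2/144) = 0.122, or 6.5% of 1.87
- Participation: 2.802 × 0.56 × √(2/144) = 0.185, or 10.9% of 1.70
- Motivation: the same 0.185, or 10.1% of 1.83

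The percentages match to the decimal. With alpha divided by three (0.0167) on the same basis, the MDDs would be 0.141, 0.214 and 0.214, which do not match. So each row was computed at an undivided 0.05.

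**3. Error rate if all three were treated as primary**

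This assumes that any one of three two-sided tests at 0.05 would count.
- Independent tests: 1 − 0.95³ = 0.143
- Equal correlation among three normal test statistics (simulation, one million draws each): 12.5% at 0.5, 10.9% at 0.7, 9.8% at 0.8, 8.4% at 0.9

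The document gives no correlations, so these are assumptions. The outcomes section describes motivation and participation as two of five categories in the 24-item scale. A clearly positive correlation with the total is therefore likely, and independence is an upper bound rather than a realistic case.

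**4. Does the 80% statement survive for the total alone?**

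Table 3 plans 24 per condition in each of three counties: 3 × 24 = 72 per arm, 144 in all. With 72 per arm, √(2/72) = 1/6.
- MDD for the total: 2.802 × 0.37 / 6 = 0.173 (9.2% of 1.87), against the stated 0.12
- Power at 0.12: standard error 0.37/6 = 0.0617; 0.12/0.0617 = 1.946; 1.946 − 1.960 = −0.014; power about 49%
- One-sided at 0.05, the MDD is still 0.153

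The ratio 0.173/0.122 is √2, so 0.12 would be right with 72 per arm only if the variance were halved. Baseline adjustment would do this at a pre–post correlation of about 0.71 (1 − 0.71² ≈ 0.5), and a change score at 0.75 (2 × (1 − 0.75) = 0.5). The power section states neither. It says that an ICC was allowed for but gives no value.

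**The case against.** The strongest reply is that the power section does not define endpoints. The two places that do, the abstract and the outcomes section, agree on the total, and the data analysis section keeps primary and secondary outcomes apart. On this view the plural in the power section is loose wording; the same paragraph also speaks more vaguely of variables of primary interest.

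Much of this stands. A reader might infer that the trial may claim success on any of three tests at 0.05. The document does not support that: it states no such rule, and under the single primary outcome there is no family-wise inflation on this account. The lack of a multiplicity rule is not a fault either, since a condensed article may leave it to an analysis plan that is not shown.

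A reader might also infer that the subscales are not separate hypotheses because they form part of the total. That does not follow. They are two of five categories, and either could change while the total does not.

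The reply does not remove the conflict. The primary label on the subscales appears in a table title and again in the power sentence. An unseen analysis plan might rank the outcomes, but the published protocol would still contradict itself.

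**Conclusion.** The protocol article is wrong as written on one limited point: two outcomes that it defines as secondary are labelled primary in the power section and in Table 4. This leaves the status of a positive subscale with a null total open to dispute; it does not grant an any-of-three claim.

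The error rates in the working are conditional on treating all three as primary, and on assumed correlations. If the sponsor did mean all three to be primary and used Bonferroni, power at the stated MDDs would fall from 80% to about 65–66% on Table 4's own arithmetic basis. The choice of hierarchy therefore affects the power claim as well as the label.

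The 80% statement is a separate weakness in the same sentence. It does not follow from 72 per arm and the tabulated SD for the total unless an unstated reduction in variance is justified.

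**What to change.** Retitle Table 4 along the lines of *MDDs for the primary outcome (Mobilization total) and two secondary subscales*. In the power text, change the plural to the primary outcome. Mark the Participation and Motivation rows as secondary; they may stay in the table, since giving detectable differences for secondary outcomes is acceptable.

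Before the 80% sentence is kept, even for the total alone, recompute the MDD for 72 per arm, or state and justify the variance reduction and the ICC that lead to 0.12.

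The relabelling costs a table title, a sentence and two row labels. It needs no change to sample size, data collection or model. The price is that the subscales can no longer be presented as primary. The power check may show a larger detectable difference than the one now printed.

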### Data analysis

For the survey data, descriptive univariate analyses will be conducted on all study variables. The data will be checked for outliers, violations of normality and missing data. Predictors of drop-out and nonresponse will be explored to better understand any discernible systematic processes in play, taking advantage of the data collected until the last time point and demographic variables. If the missing data are found to be random and ignorable, multiple imputations will be used to address missing data [42]; otherwise, an intent-to-treat approach that makes full use of available data in determining intervention effects will be used for all analyses.

Scale scores will be calculated for all outcomes. The first step will be to calculate the intraclass correlation coefficient (ICC) to determine what percentage of the variance in the dependent variable is attributed to being from the same community. If the ICC at the community level is negligible, the community will not be used in the nested structure, and robust standard errors will be estimated to correct for the nested data structure. For primary and secondary outcomes, a two-level clustered longitudinal model with growth trajectories (change from Year 1 to Years 2 and 3) will be assessed at level 1 for each participant; variation in growth parameters among participants depending on the treatment status nested within location will be captured in the level 2 model. STATA will be used to estimate these two-level models. Covariates at different levels will be included at the two levels as predictors to isolate the effects on treatment outcomes. The two-level longitudinal model in STATA can be utilized for continuous as well as categorical and binary outcomes with minor changes in the interpretation of coefficients.

Data collected during the focus groups is for the purpose of including additional perspectives to the community research team members and Topic group members. Analysis of the data will focus on identifying themes from the information shared in the focus groups and summarizing them for discussion.

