### Implementation

In each county, a local community research team will lead recruitment and activities. The composition of each community research team is planned as follows: one local Cooperative Extension agent, one project coordinator, and four additional community stakeholders.

In SEED Method counties, the community research teams will use the *SEED Stakeholder Identification Matrices* to identify three groups of stakeholders to engage in the process. The stakeholders are divided into separate groups primarily to emphasize their different perspectives and lived experiences, as well as to maximize affinity within the groups. The three Topic groups will attend seven meetings facilitated by their local community research teams. During these seven meetings, they will learn about the SEED Method process; review and discuss data about opioid use, opioid misuse, local statistics, and services; review focus group data from other stakeholders in their community; discuss relevant themes; engage in participatory conceptual modeling to explore potential causal factors and their interrelationships; participate in facilitated strategy development and strategy prioritization activities; and discuss community action planning. For each of the seven planned meetings, the Topic groups will meet separately; thus, each will develop their own conceptual models and list of prioritized strategies.

In the Delphi county, the community research team will identify which stakeholders to include in the intervention using discussion-based consensus. They will also finalize the contents of the surveys to be used to solicit information from participants via the Delphi method. Delphi participants will attend an introductory meeting facilitated by the local community research team to learn about the Delphi method; review and discuss data about opioids, opioid misuse, local statistics, and services. They will then receive an online survey asking them to identify strategies and a second online survey asking them to prioritize strategies. After each survey, they will receive a summary of the findings by email. The community research team will bring all Delphi participants together again to discuss the results and community action planning. All stakeholders will participate in the surveys and group meetings together, thus developing one set of strategies.

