## Discussion

With the increasing popularity of community engaged research, there is an urgent need for data on the effectiveness of different engagement methods to help researchers and community partners make decisions about which methods are best suited to their needs. This research protocol describes a study comparing the effectiveness of two community engagement methods, the SEED Method and the Delphi method, and a control intervention. Participants in three rural counties will create local strategies for addressing opioid misuse and prioritize those strategies for use in community action planning. Community members participating in the study represent a range of relevant stakeholders. We will assess changes in the self-rated civic engagement of participants and compare the number and types of strategies created and prioritized using the three methods evaluated. This protocol describes a group randomized controlled trial to evaluate the effectiveness of these methods on increasing the civic engagement of participants and on the number, quality, and type of strategies created. Given the design of the study, we will be able to compare the SEED Method to the Delphi Method and compare both of these methods to the control group. We will also be able to explore how effects differed depending on participant role (community research team member, intervention/control group participant, and focus group participant).

The strengths of this protocol include replicating the implementation of the SEED Method, which was previously used in a rural Virginia county and a large midwestern city, to develop community strategies for reducing opioid misuse. Furthermore, we will use a rigorous randomized design with data collected at three time points. While the protocol was developed collaboratively with the previous developers of the SEED Method, an independent evaluation team will collect and analyze the data. Limitations could include the small sample size and the use of a relatively new outcome measure (the Mobilization Scale). Further limitations could result from the ability to recruit and retain the target number of participants in the rural communities. While we have specified recruitment targets and project activities, this is community-led research, and some decision-making will take place during implementation by community teams, which is considered a normal part of the process.

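### The planned model examines clustering by community only and has no term for the meeting groups that deliver the intervention, so the intervention-versus-control standard error is too small if outcomes correlate within those groups

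*Protocol article*

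**What the plan says.** **Randomisation.** The Randomization section of the protocol article randomises individuals, eight at a time, within a specific group. The Recruitment section says the controls contain equal numbers from each stakeholder group. The Discussion nevertheless states: "This protocol describes a group randomized controlled trial".

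**Delivery.** Table 3 plans three groups of 8 in each of the two SEED counties and one group of 24 in the Delphi county. For all seven SEED meetings, the Implementation section says "the Topic groups will meet separately; thus, each will develop their own conceptual models and list of prioritized strategies". Delphi participants take their surveys and meetings as one body. Controls receive two online surveys and hold no meetings.

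**Analysis.** The first step in the Data analysis section is to "determine what percentage of the variance in the dependent variable is attributed to being from the same community". If that ICC is negligible, community leaves the nested structure and robust standard errors are used; the cluster unit is not named. The model has occasions within participants at level 1. At level 2, growth varies between participants by treatment arm within location.

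**Power.** The Sample size and power analysis section works by "setting the alpha error at 0.05 and the beta error at 0.20" and says it adjusts for an estimated ICC. It gives neither the value nor the level of that ICC. Table 4 is headed "Estimated *n* = 144".

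**The concern.** This is an individually randomised trial in which one arm is treated in groups. Participants who start out independent may become alike because they share a facilitator, discussions and group dynamics over the course of the intervention. The protocol gives reason to expect this: Topic groups are formed for affinity, the surveys measure how the group works, and the outcome is civic mobilisation.

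The correlation arises in the intervention arm at the level of the meeting group. The plan looks for it at the level of the county. Both arms are present in every county, so an additive county effect cancels from intervention versus control. Adjusting for county therefore does not account for the meeting groups. If within-group correlation is present and ignored, the 72 intervention participants are counted as 72 independent observations. Intervals for the primary outcome are then too narrow and the false-positive rate exceeds the nominal 5%.

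**Working it through.** **1. The plan's own figure.** Inputs from the Sample size and power analysis section: SD 0.37 and mean 1.87 for the Mobilization Scale total, alpha 0.05 (taken as two-sided), power 80%, and 24 per condition in three counties, so 72 per arm.

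MDD = (1.960 + 0.842) × SD × √(2/n per arm)

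- 72 per arm: 2.802 × 0.37 × √(2/72) = 0.173 (9.2% of 1.87). One-sided, it is 0.153 (8.2%).
- 144 per arm: 2.802 × 0.37 × √(2/144) = 0.122 (6.5%).

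Table 4 states 0.12 (6.5%). All three rows of the table reproduce with 144 per arm and no ICC inflation, and not with 72 per arm. At 72 per arm, power for a difference of 0.12 is about 49%. A halved variance, for example from baseline adjustment with a correlation of about 0.71, would give the same figures at 72 per arm, but none is stated. The baseline used below is therefore 0.173.

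**2. Effect of ignoring the meeting groups.** Let ρ be the ICC within a meeting group, for the change that the model estimates. It is an assumption; the article gives no value. Controls are taken as independent.

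- Mean of (group size − 1) over intervention participants: (48 × 7 + 24 × 23)/72 = 888/72 = 12.33.
- Intervention-arm design effect: 1 + 12.33ρ.
- Variance inflation of the contrast: (1 + 1 + 12.33ρ)/2 = 1 + 6.17ρ.
- Type I error: 2 × [1 − Φ(1.96/√inflation)].
- MDD: 0.173 × √inflation.

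| Assumed ρ | Design effect, intervention arm | Variance inflation | True SE / naive SE | Type I error | MDD, 72 per arm |
|---|---|---|---|---|---|
| 0 | 1.00 | 1.00 | 1.00 | 5.0% | 0.173 |
| 0.01 | 1.12 | 1.06 | 1.03 | 5.7% | 0.178 |
| 0.02 | 1.25 | 1.12 | 1.06 | 6.4% | 0.183 |
| 0.05 | 1.62 | 1.31 | 1.14 | 8.7% | 0.198 |
| 0.10 | 2.23 | 1.62 | 1.27 | 12.3% | 0.220 |

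The MDDs use normal quantiles, so they leave out the further cost of small-sample degrees of freedom.

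**3. Does adjusting for county help?** In 20,000 simulated null trials per ICC, with change scores and county as a fixed effect, type I error was 5.3% at ρ = 0. It was 6.4%, 8.8% and 12.6% at ρ = 0.02, 0.05 and 0.10. Adjusting for county does not repair it.

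**4. By method.** Variance inflation is 1 + 3.5ρ for SEED versus control and 1 + 11.5ρ for Delphi versus control. At ρ = 0.01, 0.02, 0.05 and 0.10, type I error is 5.4%, 5.8%, 7.1% and 9.2% for SEED, and 6.3%, 7.7%, 11.8% and 18.1% for Delphi.

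**5. Allowing for stakeholder strata.** Because randomisation is within stakeholder group, variance shared by both arms of a stratum cancels from the contrast. If strata explain a share s of outcome variance and are left out of the model, the inflation becomes 1 − s + 6.17ρ (pooled) or 1 − s + 3.5ρ (SEED). With an assumed s = 0.10:

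- ρ = 0.02: 0.9 + 0.123 = 1.023, type I error 5.3%. For SEED alone, 0.9 + 0.07 = 0.97, giving 4.7%.
- ρ = 0.05: 0.9 + 0.308 = 1.208, type I error 7.5%. For SEED alone, 0.9 + 0.175 = 1.075, giving 5.9%.

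**The case against.** **The ICC is assumed.** This stands. A reader might infer that the standard error is certainly and seriously too small. The documents do not support that: they give no meeting-group ICC, and at 0.01 to 0.02 the inflation is small. If strata are also left out of the model, it can vanish or reverse at small ICCs (step 5).

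**Robust standard errors may cover it.** The cluster unit could turn out to be the meeting group. But the fallback applies only when the community ICC is negligible, and the unit could equally be the participant or the county. Clustering on county would leave three clusters, too few for a robust variance.

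**The level 2 wording may cover it.** Treatment within location can be read as an arm-by-county term. In the Delphi county that cell is the single meeting group, which supplies 552/888 = 62% of the multiplier. Even if the Delphi group were fully absorbed, the six Topic groups leave a multiplier of 336/72 = 4.67 and a type I error of 6.4% at ρ = 0.05 and 7.8% at ρ = 0.10. An arm-by-county term cannot separate three Topic groups within a county, and three locations would estimate it poorly.

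**Community is not irrelevant.** This stands in part. County cancels from intervention versus control only. SEED versus Delphi is a comparison between counties, where it does not cancel.

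**This is detail for an analysis plan.** The exact degrees-of-freedom method is. The clustering level is not, because the article chooses it, gives a rule for dropping it and fixes the model levels.

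**Conclusion.** The point holds conditionally. As written, the plan has no term for the level at which the intervention is delivered. For any positive meeting-group ICC, with the strata accounted for, it understates the standard error of intervention versus control. Type I error is about 5.7% to 6.4% at an ICC of 0.01 to 0.02, and 8.7% to 12.3% at 0.05 to 0.10. The effect is modest in the first range and material in the second. These figures assume planned group sizes, independent controls and equal total variance in the two arms; unmodelled strata lower them.

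Two further inferences are not supported. The Discussion's label might suggest that groups were randomised, but the Randomization section is clear that individuals are. Table 4 might be thought to rest on a community ICC, but the article names no level.

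With one Delphi group in one county, no model can separate the group effect or the county effect from the effect of the Delphi method. The Discussion says, without this limit, that the two methods can be compared.

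**What to change.** - Describe the trial as individually randomised with group treatment.
- Include the randomisation strata (county by stakeholder group) in both arms.
- Add a random effect for meeting group in the intervention arm only (a partially nested model), with small-sample degrees of freedom. If robust standard errors are kept in any branch, name the cluster unit.
- State that neither the group effect nor the county effect can be separated from the Delphi effect, and present SEED versus Delphi as descriptive.
- State the level and value of the ICC used for Table 4, and restate the MDDs for 72 per arm over a range of meeting-group ICCs. For the total score, the range 0.01 to 0.10 gives 0.178 to 0.220 before any small-sample penalty.

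The cost is a change of wording and a meeting-group identifier that the allocation already provides. Intervals will be somewhat wider and the MDDs less favourable.

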### Interventions

Two counties will use the SEED Method and one county will use a modified Delphi method. We were originally funded to implement the SEED Method in three counties but decided to implement the Delphi method in one county for comparative and logistical reasons.

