### Recruitment

Recruitment will occur through a combination of outreach strategies, including personal contacts, flyers and messages sent to partner organizations to be shared with potential participants, social media postings or advertisements, and advertisements in local media. The outreach materials will provide contact information for the study coordinator. The study coordinator will review eligibility criteria with potential participants and confirm eligibility for a specific stakeholder group within the relevant site. Once deemed eligible, the research coordinator will obtain informed consent. The target is 48 participants per county (144 total) divided as follows: 24 in the intervention group (For the SEED Method they are further divided into three stakeholder Topic groups) and 24 in the control group (composed of an equal number of stakeholders from each group). These are our target numbers, but flexibility will be allowed which may result in some stakeholder groups being larger or smaller than the target based on the community research teams’ ability to recruit.

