### Randomization

A member of the evaluation team will randomize when there are eight consented participants in a specific group. Each of the eight consented participants will be assigned a unique number from one to eight. Using the “Sequence Generator” from random.org, participants will be randomized to an intervention or control group. This process will be repeated until each intervention group/control group has the target number of participants.

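### An ICC from three counties decides whether county stays in the primary model, and the robust-SE fallback has a type I error of about 19% if clustered on county and tested against a normal reference

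*Protocol article*

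**What the plan says.** The protocol article fixes a sequence in its Data analysis section. An ICC is computed for the share of outcome variance due to community. If it is negligible (no cut-off given), "the community will not be used in the nested structure, and robust standard errors will be estimated to correct for the nested data structure". The main model is a two-level growth model in Stata, in which variation in growth among participants "depending on the treatment status nested within location will be captured in the level 2 model". Covariates at both levels are promised but not listed.

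Other sections give the design this analysis must match:

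- Interventions: "Two counties will use the SEED Method and one county will use a modified Delphi method".
- Recruitment and Table 3: 48 participants per county, 24 intervention and 24 control in each, with controls drawn equally from the stakeholder groups.
- Randomization: a member of the evaluation team will "randomize when there are eight consented participants in a specific group", and this is repeated until the targets are met.
- Table 3: the SEED counties have three groups of eight. The number of stakeholder groups in the Delphi county is not yet set.
- Sample size and power analysis: planning assumes "setting the alpha error at 0.05 and the beta error at 0.20".

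**The concern.** The article states a rule here; it does not merely leave detail to an analysis plan. Three features of the rule cause trouble.

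1. A between-county variance estimated from three units is too imprecise to choose a model, so the form of the primary analysis would be partly chance and settled after outcome data are seen.
2. The fallback is said to correct for the nesting. In a sentence about community, that most naturally means errors clustered on county. With three clusters such errors are very unstable, and a normal reference makes the test far too liberal.
3. The model text does not match the randomisation. Both arms are present in every county, so intervention versus control is crossed with county; only SEED versus Delphi is nested in it. Individuals are allocated within stakeholder group within county, which makes those groups the strata, yet no analysis term refers to them.

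At stake is the p-value for intervention versus control on the primary outcome.

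**Working it through.** **The plan's own figures.** For the robust-error step the plan states nothing beyond the nominal alpha of 0.05, which is the benchmark below. Its only computed figure is the minimum detectable difference of 0.12 in Table 4. With 72 per arm, (1.960 + 0.842) × 0.37 × √(2/72) = 0.173, so 0.12 is not reproduced; 144 per arm would give 0.122. That is a separate matter and does not bear on this point.

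**Inputs.** From the article: G = 3 counties, 24:24 in each, individual randomisation. Assumed, because not stated: two-sided testing, the ICC values, a cut-off of 0.02 for negligible, and the clustering unit and reference distribution (varied below).

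**Step 1: can the gate work?** Take one outcome per person and the analysis-of-variance ICC with 48 per county. The estimate is (F − 1)/(F + 47), which falls below 0.02 when F < 1.94/0.98 = 1.980. If the true ICC is ρ, F is distributed as k × F(2, 141) with k = (1 + 47ρ)/(1 − ρ). For 2 numerator df, P(F(2, 141) < x) = 1 − (1 + 2x/141)^(−70.5).

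| True ICC | k | x = 1.980/k | P(estimate below 0.02) |
|---|---|---|---|
| 0 | 1.000 | 1.980 | 86% |
| 0.05 | 3.526 | 0.561 | 43% |
| 0.10 | 6.333 | 0.313 | 27% |

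So an ICC of 0.05 is called negligible in 43% of trials and one of 0.10 in 27%. A true ICC of zero exceeds the cut-off in 14%. Simulation (8,000 runs each) gave the same percentages.

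**Step 2: errors clustered on county, normal reference.** With equal counties balanced by arm, the pooled effect is the mean of three county differences. The clustered variance with the factor G/(G − 1) = 3/2 is the usual variance of that mean. The Wald statistic therefore follows t with 2 df:

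P(|t₂| > 1.96) = 1 − 1.96/√(2 + 1.96²) = 1 − 1.96/2.417 = 18.9%.

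Without the 3/2 factor the effective cut-off is 1.96 × √(2/3) = 1.600:

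1 − 1.600/√(2 + 1.600²) = 1 − 1.600/2.136 = 25.1%.

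Simulation of the first form gave 19–20% for a single outcome and 18.4–18.9% for a three-wave slope. It hardly changed for ICCs from 0 to 0.10, because county main effects cancel within counties.

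**Step 3: other readings of the same sentence.**

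| Analysis | Type I error |
|---|---|
| County-clustered, normal reference | about 19% |
| The same, without the 3/2 factor | about 25% |
| County-clustered, t on 2 df | about 5% |
| Participant-clustered, three waves | 5.1–5.4% |
| County fixed effects | 5.1–5.4% |
| County by stakeholder-group fixed effects | 5.1–5.3% |

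The t(2) version needs a critical value of 4.30. An effect with 80% power under a normal test has a standardised size of 1.960 + 0.842 = 2.80. A noncentral t with 2 df and noncentrality 2.80 exceeds 4.30 in absolute value with probability 35%, so power falls from 80% to about 35%.

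**Step 4: leaving out the strata.** Assume a county ICC of 0.05 and a stakeholder-group variance share of 0.10. An individual-level test that ignores both rejects 3.5% under the null, against 4.7% with county by stakeholder-group fixed effects. The error is conservative.

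**The case against.** The strongest reply is that the article names neither a clustering unit nor a reference distribution. Once community is removed, the nesting that remains is repeated surveys within participant, and errors clustered there hold about 5%. This stands. A reader might infer that 19% is the error rate of the protocol; it is the rate under one natural reading, and the text permits roughly 5% to 25%.

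A reader might also infer that both branches of the gate are invalid. That is not shown. County effects cancel from a contrast balanced within county: dropping county and using heteroscedasticity-robust errors rejects about 4–5% under the null. A poorly estimated random county variance mainly affects between-county terms.

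Nor does the plan simply ignore county. Location appears at level 2 when the gate does not drop it, and unlisted covariates are ordinary content for an analysis plan. The criticism is fair for the branch that drops county, and for stakeholder group, which no term names. The word nested is also right for SEED versus Delphi.

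Finally, one might expect stratum intercepts to sharpen the primary result. In a three-wave random-slope check they left the arm-by-time estimate unchanged and its standard error within 0.05% (ratio 1.0005). Strata bear on a change contrast only if they interact with time.

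What remains is the gate itself, and a stated correction whose natural reading fails with three clusters.

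**Conclusion.** The concern holds in conditional form. An ICC on 2 degrees of freedom with no threshold should not choose the primary model; with an assumed cut-off of 0.02 it would call an ICC of 0.05 negligible in 43% of trials. If the fallback errors are clustered on county and tested against a normal reference, type I error for intervention versus control is about 19%, or about 25% without the small-sample factor. Participant clustering restores about 5%. County clustering with t on 2 df does too, but with a large loss of power. Omitting stakeholder group within county is a separate, conservative fault that costs precision; the two should not be added together.

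The 5% quoted for the sound alternatives assumes no county-by-treatment variation and no effect shared within a Topic group. Assumed county-by-treatment variation with an SD of 0.2 outcome SDs raises the fixed-effect test to about 10–11%, so this assumption should be stated openly.

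**What to change.** In the Data analysis section:

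1. Delete the ICC gate and report the ICC descriptively only.
2. Fit county, and stakeholder group within county, as fixed effects whatever the ICC, with their interactions with time so that they bear on change. List the Delphi county's groups once they are set.
3. Describe intervention versus control as crossed with county, and only SEED versus Delphi as nested in it.
4. Do not use standard errors clustered on the three counties. Base inference on the participant-level mixed model (REML with Kenward-Roger or Satterthwaite degrees of freedom) or on participant-clustered errors, and name which.
5. State that the nominal 5% assumes no county-by-treatment variation and no shared Topic-group effect.

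The cost is a few sentences and a few degrees of freedom out of 144 participants. Recruitment, randomisation and data collection are unchanged.
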